## Abstract

**Background:**

Achilles tendinopathy (AT) is a common overuse injury in running-related sports where patients experience pain and impaired function which can persist. A graded rehabilitation program has been successful in reducing pain and improving function to enable a return to sport. The aim of this study is to compare the effectiveness of a criteria-based rehabilitation program including strength and reactive strength targets, with a previously successful rehabilitation program on changes in pain and function using the Victorian Institute of Sport Assessment-Achilles (VISA-A) questionnaire. Secondary aims will be to assess changes in calf strength, reactive strength, and lower limb running and forward hop biomechanics over the course of a 12-week rehabilitation program, and long-term follow-up investigations.

**Methods:**

Sixty eligible participants with chronic mid-portion AT who train in running-based sports will be included in this study. They will be randomly assigned to a group that will follow an evidence-based rehabilitation program of daily exercises with progression guided by symptoms or a group performing 3 high-intensity rehabilitation sessions per week with individualised load targets progressing to reactive strength exercises. Testing will take place at baseline, week 6 and 12. Plantar flexor peak torque will be measured using isokinetic dynamometry, reactive strength will be measured using a drop jump and lower limb biomechanical variables will be measured during a single leg forward hurdle hop test and treadmill running using 3D motion analysis. Follow-up interviews will take place at 6, 12 and 24 months after beginning the program which will assess patient participation in sport and possible re-injury.

**Discussion:**

This is the first study to propose an individualised criteria-based graded rehabilitation program in patients in with chronic mid-portion Achilles tendinopathy where progression is guided by strength and reactive strength outcome measures. This study will provide a comprehensive assessment of plantar flexor strength, reactive strength and lower limb biomechanical variables in running and forward hopping with the VISA-A questionnaire as the primary outcome measure and long term post-intervention follow-up assessments performed.

**Trial registration:**

ClinicalTrials.gov (ID: NCT04384874). Registered retrospectively on April 23rd 2020.

**Supplementary Information:**

The online version contains supplementary material available at 10.1186/s12891-021-04553-6.

## Background

The Achilles tendon is the largest and strongest tendon in the human body [1] and usually withstands very high tensile forces during exercise [2], but is also one of the most commonly injured tendons [3]. Achilles tendinopathy (AT) affects 2% of the general population [4], and has an incidence of 7–9% in running-based sports with a cumulative lifetime incidence of up to 52% among certain athletic populations [5].

Tendinopathy is described as pain and impaired function in the affected tendon [6–8]. Over time this may result in reduced physical activity, absenteeism from sport and impaired quality of life [8]. Histologically and biochemically pathological tendon has been shown to include increased hyper-cellularity, reduced collagen type I and increased type III content, increased proteoglycans and glycosaminoglycans, and blood vessel in-growth [9, 10]. Excessive loading of the tendon is believed to be the primary contributory factor to Achilles tendinopathy [11]. The fibroblastic cells known as tenocytes within the extracellular matrix are sensitive to mechanical loading and, when the tendon is overloaded, the cells alter the protein composition of the matrix resulting in pathology and reduced capacity for exercise [12].

Patients with AT usually present with pain, swelling and impaired performance of the tendon [13], as well as altered function of the plantar flexor muscles [14–16]. In a sporting population, training load perturbations such as a rapid increase in training volume, intensity or frequency are said to be common contributory factors [17]. Re-injury rates are high, most likely due to incomplete restoration of muscle-tendon unit function [18], and symptoms can persist for a number of years in some cases [19]. In an eight-year follow-up study, 20% of patients still experienced impaired physical activity [20]. A failed healing response and degenerative changes are associated with the development of chronic tendinopathy resulting in reduced load capacity and persistent pain symptoms [8]. This is described by Cook et al. [8] in their proposed continuum model involving three stages: reactive tendinopathy, tendon disrepair and degenerative tendinopathy.

Impairments in tendon mechanical properties such as stiffness and Young’s modulus have been highlighted in AT [21–23]. Wang et al. (2012) observed reduced stiffness and increased hysteresis of the Achilles tendon, along with reduced rate of force development of the plantar flexor muscles and reduced single leg horizontal hop performance in symptomatic limbs of patients with AT, compared to the non-symptomatic limb. While one study found reduced lower limb stiffness in the injured limb of runners with AT during hopping [24], biomechanical variables such as leg and joint stiffness in running and hopping tasks have not been extensively researched in patients with Achilles tendinopathy.

Many passive treatment therapies such as injections [25, 26], Non-Steroidal Anti-Inflammatory Drugs (NSAIDs) [10, 27], ultrasound [10, 27], shockwave [28, 29], laser [27], iontophoresis [25], acupuncture [30], orthotics [25, 29], wearing a night splint [31], vibration and cryotherapy [32], ﻿mucopolysaccharides [33], and a wait-and-see approach [28] have been used in the management of AT. However, there is strongest evidence for the use of exercise therapy as the primary treatment option [34–36]. Tendons adapt to exercise as the mechanical perturbation of the inter- and intra-fascicular cells triggers a molecular response signalling an expression of important proteins in the extra-cellular matrix which restore the mechanical properties of the tendon [37, 38]. Three main modes of exercise have been widely used, each associated with improvements in clinical symptoms to varying degrees, namely: Alfredson’s eccentric protocol [39], Silbernagel’s combined concentric-eccentric protocol [36] and the Heavy Slow Resistance protocol [40]. The Silbernagel protocol [see Table 1] comprises a combined concentric-eccentric exercise program performed daily, before progressing to plyometric exercises as symptoms permit, with no individualisation of exercise prescription and progression guided solely by pain symptoms on a numeric pain rating scale (NPRS).

**Table 1 Tab1:** Silbernagel’s combined concentric-eccentric program

Phase 1: Weeks 1–2	
**Patient status:** Pain and difficulty with all activities, difficulty performing 10 single leg heel raises	
**Goal:** Start to exercise, gain understanding of their injury and of pain monitoring model	
**Treatment program:** Perform exercises every day:	
• Pain monitoring model information and advice on exercise activity	
• Circulation exercises (moving foot up and down)	
• Double leg heel raises standing on the floor (3 × 10–15 repetitions)	
• Single leg heel raises standing on the floor (3 × 10)	
• Sitting heel raises (3 × 10)	
• Eccentric heel raises standing on the floor (3 × 10)	
**Phase 2: Weeks 2–5**	
**Patient status:** Pain and difficulty with all activities, difficulty performing 10 single leg heel raises	
**Goal:** Start to exercise, gain understanding of their injury and of pain monitoring model	
**Treatment program:** Perform exercises every day:	
• Pain monitoring model information and advice on exercise activity	
• Circulation exercises (moving foot up and down)	
• Double leg heel raises standing on the floor (3 × 10–15 repetitions)	
• Single leg heel raises standing on the floor (3 × 10)	
• Sitting heel raises (3 × 10)	
• Eccentric heel raises standing on the floor (3 × 10)	
**Patient status:** Pain with exercise, morning stiffness, pain when performing heel raises	
**Goal:** Start strengthening	
**Treatment program:** Perform exercises every day:	
• Double leg heel raises standing on the edge of a step (3 × 15)	
• Single leg heel raises standing on the edge of a step (3 × 10)	
• Sitting heel raises (3 × 15)	
• Eccentric heel raises standing on the edge of a step (3 × 15)	
• Quick-rebounding heel raises (3 × 20)	
**Phase 3: Weeks 3–12 (longer if needed)**	
**Patient status:** Tolerates phase 2 exercise program well, no pain at distal portion of tendon, possibly increased or decreased morning stiffness	
**Goal:** Heavier strength training, increase or begin running and/or jumping	
**Treatment program:** Perform exercises every day with heavier load 2–3 times per week	
• Single leg heel raises standing on the edge of a step with added weight (3 × 10)	
• Sitting heel raises (3 × 15)	
• Eccentric heel raises standing on the edge of a step with added weight (3 × 15)	
• Quick-rebounding heel raises (3 × 20)	
• Plyometric training	
**Phase 4: Weeks 12–6 months (longer if needed)** **Patient status:** Minimal symptoms, morning stiffness but not every day, can participate in sports without difficulty	
**Goal:** Heavier strength training, increase or begin running and/or jumping	
**Treatment program:** Perform exercises every day with heavier load 2–3 times per week	
• Single leg heel raises standing on the edge of a step with added weight (3 × 10)	
• Eccentric heel raises standing on the edge of a step with added weight (3 × 15)	
• Quick-rebounding heel raises (3 × 20)	

Recent evidence suggests that magnitude of loading, irrespective of contraction mode, is the primary stimulus for tendon adaptation [41]. Isometric exercises using 5 × 45 s contractions at 70% maximal voluntary contraction (MVC) have been used for early management of tendinopathies with evidence suggesting an analgesic effect [42]. However, this has been since contested by the findings of O’Neill et al. [43]. Documented timeframes for rehabilitation interventions vary between 6 weeks to several months with no clear objective measures for return to sport. Patients with AT display impaired reactive strength qualities during hopping tasks and it is recommended to include plyometric training at an advanced stage of a rehabilitation program to prepare for the stretch-shortening cycle demands of running-based sports [19, 36]. A multi-stage rehabilitation program that includes the combination of strength development and plyometric training may thus be beneficial, but there is a lack of consensus on assessing these qualities to guide exercise prescription and progression through the rehabilitation pathway.

While numerous studies have shown positive clinical improvements and tendon adaptations to exercise [36, 39–41, 44], studies which investigate a periodised return to sport rehabilitation program with load targets and outcome measures for progression, are necessary due to the individualised nature of its initial presentation and diverse timeframes for recovery. The Sports Surgery Clinic (SSC) rehabilitation pathway [see Table 2] proposed in this study involves 6 stages of progressive rehabilitation (SSC6) from initial diagnosis and assessment, through developing strength, power and reactive strength, linear and multi-directional running, and return to performance. The existing literature has demonstrated positive clinical outcomes using Silbernagel’s rehabilitation program [18, 44] and we have selected this a suitable comparative control for this study which involves a graded progression pathway from combined concentric-eccentric exercises to plyometric training [36].

**Table 2 Tab2:** SSC6 Rehabilitation program

Level 1 *Week 0–3* Entry criteria: Pain > 5/10 on SL calf raise	Kinetic chain (2 days per week) Box squat 3 × 8 reps @ 10RM Step-up 3 × 8 reps e/s @ 10RM	Calf Isometrics (daily) 5 × 45 s holds @ 60 s RM)		
Level 2 *Week 0–4* Entry criteria: Pain < 5/10 on SL calf raise	**Kinetic chain (2 days per week)** Front squat 4 × 8 reps @ 10RM Or Deadlift 4 × 8 reps @ 10RM Step-up 3 × 8 e/s @ 10RM Or Split squat 3 × 8 reps e/s	**Calf strength** (3 days per week) SL calf raises 4 × 8 reps @ 10RM *~ Begin with dumbbell and shoes off* *~ Aim to through 1st MTPJ and good rearfoot control* Seated SL calf raises 4 × 10 reps @ 12RM *~ Begin with kettlebell on knee and forefoot on a plate*		
Level 3 *Week 3–6* Entry criteria: Pain < 4/10 on SL calf raise	**Kinetic chain (2 days per week)** Front squat 4 × 6 reps @ 8RM Or Deadlift 4 × 6 reps @ 8RM Step-up 3 × 6 e/s @ 8RM Or Split squat 3 × 6 each side @ 8RM	**Calf strength** (3 times per week) SL calf raises 4 × 8 reps @ 10RM *~ Progress to a smith machine or barbell using rack for support* *~ Aim for > 70% BW* Seated SL calf raises 4 × 10 reps @ 12RM *~ Progress to smith machine or landmine press* *~ Aim for > 90% BW*	**Coordination/running technique** Ankling 3 × 10 m March 3 × 10 m A-skip 3 × 20 m	
Level 4 *Week 6–9* Entry criteria: Pain < 5/10 for 10 DL hops < 10% asymmetry in calf isokinetic tests	**Kinetic chain (2 days per week)** Front squat 4 × 6 reps @ 8RM Or Deadlift 4 × 6 reps @ 8RM Step-up 3 × 6 reps e/s @ 8RM Or Split squat 3 × 6 each side @ 8RM	**Calf strength** (3 times per week) SL calf raises 4 × 8 reps @ 10RM *~ Progress to a smith machine or barbell using rack for support* *~ Aim for > 80% BW* Seated SL calf raises 4 × 10 reps @ 12RM *~ Progress to smith machine or landmine press* *~ Aim for > 110% BW*	**DL Reactive strength** (2 times per week) DL Pogo hops in-place 4 × 10 (Day 1) *~ Keep knees straight and stiff* *~ Flat foot contacts* *~ Active dorsiflexion during flight phase* DL pogo hops forward 4 × 10 (Day 2) ~ *Keep knees straight and stiff* *~ Flat foot contacts* *~ Active dorsiflexion during flight phase*	
Level 5 *Week 9–12* Entry criteria: Pain < 4/10 for 10 SL hops Exit criteria: < 10% asymmetry in single leg vertical and horizontal RSI	**Kinetic chain (2 days per week)** Front squat 3 × 5 reps @ 7RM Or Deadlift 3 × 5 reps @ 7RM Step-up 3 × 5 reps e/s @ 7RM Or Split squat 3 × 5 each side @ 7RM	**Calf strength** (3 times per week) SL calf eccentric 4 × 8 reps @ 10RM *~ Use a smith machine/leg press/ barbell using rack for support* *~ Up on 2 legs, lower down slowly on 1 over 3 s* *~ Aim for > 100% BW or equivalent* Seated SL calf raises 4 × 10 reps @ 12RM *~ Progress to smith machine or landmine press* *~ Aim for > 110% BW*	**DL Reactive strength** (2 times per week) Drop jump 4 × 4 reps from 20 to 30 cm box ~ *Maximum jump height with minimal contact* *~ Minimal knee bend on ground contact* *~ Cue “imagine the floor is hot”*	**SL Reactive strength** (2 times per week) SL pogo hops in-place 4 × 10 e/s (Day 1) SL pogo hops forward 4 × 10 e/s (Day 2)
Level 6 *Week 12–26* Recommended maintenance program	**Kinetic chain (2 days per week)** Front squat 3 × 5 reps @ 7RM Or Deadlift 3 × 5 reps @ 7RM Step-up 3 × 5 reps e/s @ 7RM Or Split squat 3 × 5 each side @ 7RM	**Calf strength** (2 times per week) SL calf isometric 4 × 8 reps × 4 s holds *~ Use a smith machine/leg press/ barbell using rack for support* *~ Up on 2 legs, hold on 1* *~ Aim for > 140% BW or equivalent*	**DL Reactive strength** (2 times per week) Drop jump 4 × 5 reps from 20 to 30 cm box	**SL Reactive strength** (2 times per week) SL pogo hops in-place 4 × 12 e/s (Day 1) SL pogo hops forward 4 × 12 e/s (Day 2)

Abbreviations: DL - double leg, SL - single leg, reps - repetitions, e/s - each side, BW - bodyweight, RM - repetition maximum

Considering the multiple functional impairments experienced by athletes with AT, a battery of kinematic and kinetic tests to investigate plantar flexor strength, reactive strength and lower limb biomechanical variables in hopping and running, may provide guidance on exercise prescription, progression through a rehabilitation program and return to sport decision-making. To the best of our knowledge no study has assessed such breadth of athletic qualities affected by AT.

This study will aim to compare the outcome of SSC6, a multi-factorial, individualised criteria-based rehabilitation program with Silbernagel’s combined concentric-eccentric program, in physically active participants with chronic mid-portion AT. In addition to the commonly reported outcome measures of VISA-A, as secondary outcome measures we will assess plantar flexor strength, reactive strength and lower limb kinematic and kinetics during running and hopping at 6-week intervals during a 12-week rehabilitation program as these have not been reported previously. We also further aim to investigate the long term effects of rehabilitation programs and achieved outcome measures over a 6, 12 and 24-month follow-up period.

### Aims

Using the VISA-A questionnaire as the primary outcome measure, the aim of this study is to compare the effectiveness of Silbernagel’s daily exercise program with progression guided by pain symptoms, against SSC6’s exercise program carried out 3 times per week with specific load targets. We will assess plantar flexor strength using isokinetic dynamometry, reactive strength based on a drop jump, and lower limb biomechanics during a novel single leg horizontal rebound test and running, and investigate whether changes in these variables over the course of the 12-week rehabilitation program are associated with improved pain and function outcomes using the VISA-A questionnaire when comparing the two rehabilitation programs. We will assess participant satisfaction with their prescribed program, adherence and fidelity using a training diary and perform follow-up interviews at 6, 12 and 24 months to analyse participation in their sport and any potential re-injury rates.

## Methods

### Study design

This study will be a single-centre, parallel group randomized-control trial. The data collection will take place at the SSC Sports Medicine department at the Sports Surgery Clinic in Dublin. The study protocol has been reported using the Standard Protocol Items: Recommendations for Interventions (SPIRIT) statement guidelines [Available in supplementary files]. The study was approved by the Sports Surgery Clinic’s Research Ethics Committee, (Application number: SAREB13/05/19CG/MJ) and registered at ClinicalTrials.gov (ID: NCT04384874).

### Participants

Adult patients diagnosed with chronic mid-portion AT who participate in running-based sports will be invited to take part in this study. Patients who present to the Sports Surgery Clinic (SSC) with Achilles pain will be seen by a Sport and Exercise medicine physician, their history and clinical examination will be confirmed with magnetic resonance imaging (MRI). If the patient is diagnosed and meets the inclusion criteria, they will be invited to participate in the study and will be given an information sheet to read with a minimum of 24 h to consider before agreeing by signing a consent form [Additional file 2: Appendix 2]. Participants will also be recruited externally through adverts on social media channels, emails to coaching contacts and local sports clubs. Participants who feel that they are eligible and meet the inclusion criteria will be referred for examination by a sport and exercise medicine physician at the clinic to confirm diagnosis and eligibility for the study.

### Inclusion/exclusion criteria

#### Inclusion criteria

Participants will be eligible for this study if they are aged 18–45 years, perform running-based sports, are diagnosed with mid-portion AT, following a clinical examination by a sports medicine physician and confirmed with MRI, and have been experiencing symptoms for more than 3 months but less than 3 years.

#### Exclusion criteria

Patients will be ineligible for the study if they have a co-existing lower-limb injury, have had a running-related injury in the previous 12 months, or have had any peritendinous, or intra tendinous Achilles injection in the past 6 months, or previous Achilles surgery [15, 18, 44].

### Randomisation and blinding

Participants will be assessed at baseline before being randomly assigned to the intervention group or control group and will follow a prescribed rehabilitation program for 12 weeks. See Table 3 for a summary of the study design. The randomisation will be performed using the online tool www.sealedenvelope.com and the participant will be handed an envelope from an independent observer not involved with the study, containing their respective group allocation number. The principal investigator and training group investigators will be blinded to the group randomisation process. These procedures have been used in similar studies [45]. The participants will be prescribed with an exercise program with video demonstrations of each exercise under the supervision of the investigator in their respective group. The program will be carried out at home or in a local gym in addition to supervised rehabilitation sessions every 2–3 weeks at SSC. Testing will take place again at week 6 and 12. Follow-up interviews will take place at 6, 12 and 24 months after baseline testing. The investigator involved with the testing and follow-up interviews will also be blinded to the group allocation. The primary outcome measure will be changes to the VISA-A questionnaire. Secondary outcome measures will include plantar flexor strength, lower limb reactive strength, biomechanics and running gait.

**Table 3 Tab3:** Overview of outcome measures over the course of the study

	Baseline	Week 6	Week 12	6 months	12 months	24 months
Body mass	X					
Body height	X					
Body mass index	X					
Sport/activity level	X			X	X	XX
VISA-A Questionnaire	X	X	X	X	X	X
Isokinetic plantar flexor peak torque (knee extension)	X	X	X			
Isokinetic plantar flexor peak torque (knee flexion)	X	X	X			
3D running gait analysis	X	X	X			
Double leg drop jump		X	X			
Single leg drop jump		X	X			
Single leg horizontal rebound		X	X			
Exercise compliance		X	X	X		

### Outcome measures and assessments

#### Investigations

At baseline, week 6 and 12, all participants will be required to complete a VISA-A questionnaire as well as perform isokinetic testing and 3D motion capture running gait assessment. In addition, hop testing will be performed at week 6 and 12 [see Table 3]. Hop testing is included in the testing battery from week 6 onwards as it is expected some participants with Achilles pain at baseline testing may be fearful of performing hopping tasks or risk of exacerbating their pain, and the data collected may not be an accurate reflection of their capabilities.

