### Primary outcome measure

#### VISA-A questionnaire

The VISA-A questionnaire has been shown to be a valid, reliable and easy-to-use outcome measure tool for intervention studies on AT [46]. It consists of eight questions regarding pain and function during both daily living and sporting activities. The overall score is between 0 and 100 where higher scores represent reduced pain and improved function. An improvement of 21 points between 2 and 12 weeks of a rehabilitation program have been typically observed [44]. While the VISA-A score will not determine eligibility for inclusion into the study, it will be used to map progress over the course of the rehabilitation program and in the follow-up period. The difference in VISA-A score between both training protocols from baseline testing to the outcome testing at 6 weeks, 12 weeks, 3, 6 and 12 months; will formulate the primary outcome measure for this study.

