### Statistical analysis and power calculation

This study is powered to detect a change of 15 points on the VISA-A questionnaire, similar to previous studies investigating clinical changes after a rehabilitation program [61, 62]. The average reported change in a VISA-A questionnaire after a 12-week intervention is 21 points with a standard deviation 6.6 points [44]. Assuming a power of 80% and a two-sided 5% significance level, a total of 25 participants in each group would be required. Allowing for a conservative drop-out rate of 15%, the proposed total sample size is 60, with 30 in each group. This number is similar to those used in other high quality injury rehabilitation RCT studies [40, 45].

Statistical analysis will be performed using R (R Studio version 1.2.5). Descriptive statistics will be used for all continuous variables, and means and standard deviations will be reported. Comparisons between both groups at different timepoints will be assessed using Student’s independent samples two-tailed t-tests. An intention to treat analysis will be used to test a within-group and between-group change in VISA-A questionnaire score at testing and follow-up timepoints, using a repeated measures Analysis of Covariance (ANCOVA). The primary outcome measure - changes to the VISA-A questionnaire, will the dependent variable, group will the between participants factor and time will be the covariate. Non-parametric equivalents (Matt-Whitney U-Test and Friedman Test respectively) will be used if a Shapiro-Wilk test indicates that the assumption of normality has not been met. A multiple regression analysis will be used to investigate the total variance and the relative weight of each independent variable with changes in VISA-A score as the dependent variable. The independent variables will be changes in plantar flexor strength, reactive strength and lower limb biomechanical variables, as well as exercise adherence and fidelity. Effect sizes will be reported using partial eta squared threshold values of > 0.2 (small), > 0.5 (moderate), and > 0.8 (large). Statistical significance will be accepted at α = 0.05.

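### The aims and the regression need 12-week change in reactive strength and forward hop biomechanics, but hop tests are done only at weeks 6 and 12, so that change cannot be computed

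*Protocol article*

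**What the plan says.** The Abstract (Background) sets a secondary aim to "assess changes in calf strength, reactive strength, and lower limb running and forward hop biomechanics over the course of a 12-week rehabilitation program". The Aims section names the drop jump and the single leg horizontal rebound among its tests. It then asks whether "changes in these variables over the course of the 12-week rehabilitation program are associated with improved pain and function outcomes", judged by VISA-A.

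The Statistical analysis and power calculation section turns this into a multiple regression with change in VISA-A as the dependent variable: "The independent variables will be changes in plantar flexor strength, reactive strength and lower limb biomechanical variables", together with adherence and fidelity. It gives no time window for either side of the model.

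On timing, the Abstract (Methods) says "Testing will take place at baseline, week 6 and 12", then lists the drop jump and hurdle hop without exception. The Investigations section places VISA-A, isokinetic testing and running gait at all three visits, and continues: "In addition, hop testing will be performed at week 6 and 12". It explains that some participants may be afraid to hop at baseline or may aggravate their pain, and that the data might then misrepresent what they can do. Table 3 likewise marks the three hop tests at weeks 6 and 12 only.

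**The concern.** Change over a 12-week program needs a value at week 0 and a value at week 12. Reactive strength comes only from the drop jump, and forward hop biomechanics only from the hurdle hop, so without a baseline hop test neither has a 12-week change. An analysis plan can choose a window, but it cannot create a measurement that was never taken.

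The Discussion expects the results to show whether better reactive strength goes with less pain. As scheduled, the data can speak to weeks 6 to 12 only. Suppose a participant gains reactive strength and VISA-A points together in the first six weeks. If VISA-A change is taken from baseline, that participant enters the regression with a large VISA-A change and little hop change, which hides the very association being sought. There is also a reporting risk: a week 6 to 12 difference between arms could be presented as the effect of the whole program.

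**Working it through.** The protocol gives no figure to reproduce here. The check compares what each analysis needs with what Table 3 and the Investigations section provide.

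| Measure | Week 0 | Week 6 | Week 12 | 12-week change |
|---|---|---|---|---|
| VISA-A | yes | yes | yes | computable |
| Isokinetic plantar flexor torque (both knee positions) | yes | yes | yes | computable |
| 3D running gait | yes | yes | yes | computable |
| Double leg drop jump | no | yes | yes | not computable |
| Single leg drop jump | no | yes | yes | not computable |
| Single leg horizontal rebound | no | yes | yes | not computable |

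**Extent.**
- Hop tests without a baseline: 3 of 3.
- Share of the program covered by the available change: (12 − 6)/12 = 50%.
- The regression names five predictor groups: plantar flexor strength, reactive strength, biomechanics, adherence and fidelity. Reactive strength lacks a baseline entirely. Biomechanics lacks it for the hop part and keeps it for running.

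**Is week 6 a substitute for baseline?** No. It falls after randomisation and six weeks of different programs. Table 1 lists "Quick-rebounding heel raises" in Phase 2 (weeks 2–5), and Phase 3, which includes plyometric training, can start at week 3. Table 2 Level 3 (weeks 3–6) lists ankling, marching and A-skip drills. Some gain before week 6 is therefore plausible in either arm.

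**Which VISA-A change would the regression use?** The section does not say. The VISA-A questionnaire section defines change "from baseline testing to the outcome testing at 6 weeks, 12 weeks, 3, 6 and 12 months". Carried into the regression at week 12, that sets a 6-week predictor against a 12-week outcome.

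**Illustration of that mismatch (assumed values).** Let r be the correlation of hop change with VISA-A change when both cover weeks 6 to 12. Let k be the SD of week 6–12 VISA-A change divided by the SD of baseline-to-week-12 change. If hop change in weeks 6–12 is unrelated to VISA-A change in weeks 0–6, then

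observed correlation = r × k.

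Take r = 0.40 (assumed) and n = 50, the 25 per group in the sample size section. The two-sided 5% critical correlation is t/√(n − 2 + t²) with t = 2.011 on 48 df: 2.011/√(48 + 4.043) = 0.279. Power is approximately

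Φ{ [atanh(ρ) + ρ/(2(n − 1)) − atanh(0.279)] × √(n − 3) },

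where ρ is the observed correlation.

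| k | ρ | Power |
|---|---|---|
| windows matched | 0.40 | 83% |
| 0.9 | 0.36 | 74% |
| 0.7 | 0.28 | 51% |
| 0.5 | 0.20 | 29% |

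If late hop gain also correlates q with early VISA-A change (early and late VISA-A change having equal SDs and being uncorrelated), the observed correlation is (0.40 + q)/√2. This gives 0.07, 0.28 and 0.49 for q = −0.3, 0 and +0.3. The distortion can therefore go either way. These are single-correlation figures, while the planned model has several predictors, so they show direction and rough scale only.

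**The case against.** The best defence is that nothing in the protocol expressly says baseline to week 12 for hop variables. The regression speaks only of changes, and the Background says the tests are done at 6-week intervals during the program, which weeks 6 and 12 satisfy. A week 6–12 change can be computed and lies within the program, and an analysis plan that is not shown could fix the window. The baseline omission is disclosed and has a sound clinical reason. The testing sentence in the Abstract is condensed and is true of the battery as a whole. In the SSC6 arm, exercises labelled as reactive strength begin only at Level 4 (weeks 6–9), so week 6 is close to a pre-training value there. The outcomes are secondary, and the power illustration rests on assumed inputs.

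Some of this stands. The reason for not hopping at baseline is sensible and need not be reopened, the Abstract sentence is the weakest of the evidence, and the illustration should carry no weight for severity. The rest does not remove the problem. Change over the course of a 12-week program naturally means from its start, and no section redefines it for hop measures. The interval wording describes visit spacing, not the change to be analysed. The SSC6 point does not help the control arm, where plyometrics may start from week 3. The only VISA-A change defined starts at baseline, so the text as written leads to mismatched windows.

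**Conclusion.** The concern holds. The protocol promises and models a 12-week change in reactive strength and forward hop biomechanics that its own schedule makes impossible to form: 3 of 3 hop tests have no baseline, and the available change covers 6 of 12 weeks. This follows from the text and Table 3 alone and rests on no assumed number.

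The reach is limited to secondary outcomes. A week 6–12 difference between arms remains a valid randomised contrast for late gain, but it is not the total effect of the program. The possible loss or distortion in the regression depends on unknown correlations and on a VISA-A window that the analysis section leaves open. The point should be corrected before analysis, since criteria-based progression on strength and reactive strength is the trial's claimed novelty.

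**What to change.** 1. In the Abstract and Aims, state that hop measures are taken at weeks 6 and 12 only and that no 12-week change is claimed for them. Correct the testing sentence in Abstract (Methods) to match.
2. Make the week-12 value the between-arm comparison for hop outcomes, with week 6 reported separately. The analysis section already allows this: "Comparisons between both groups at different timepoints will be assessed using" t-tests. Report week 6–12 change only as late gain.
3. Remove hop change from the baseline-to-week-12 regression, which keeps strength change, running change, adherence and fidelity. Fit a second model of week 6–12 VISA-A change on week 6–12 hop change, with strength change, running change, adherence and fidelity over the same weeks. Table 3 schedules all of these at weeks 6 and 12, and the training diary is reviewed at week 6 and handed in at week 12.
4. Limit the Discussion's conclusion on reactive strength to weeks 6–12. Residual pain at week 6 may be named as a possible limitation. Adjustment for the pain ratings already collected is optional and only a sensitivity analysis, because VISA-A itself scores pain.

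The cost is wording in the Abstract, Aims, analysis section and Discussion, plus one more model to report. No new test or visit is needed. The hop model gives up the first six weeks of VISA-A change.
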